## Abstract

**Background**: Current guidelines acknowledge that early discharge is not associated with late mortality and that in-hospital length of stay (LOS) of 48–72 h should be considered following successful primary percutaneous coronary intervention (PPCI) in low-risk patients. Recent studies have highlighted the safety of very early discharge after PPCI in highly selected low-risk patients; however, objective tools to guide discharge timing remain limited. The Index of Microcirculatory Resistance (IMR) offers a quantitative assessment of microvascular function and may help identify patients suitable for very early discharge. We aimed to evaluate the feasibility of using IMR to guide very early discharge in patients who underwent uncomplicated PPCI. **Study design and objectives**: The Safety of Early Discharge Using Index Microcirculatory Resistance in Patients with Acute Myocardial Infarction (SECURE) study is designed to assess the feasibility of using IMR, measured immediately following successful PPCI, to guide early discharge from hospital within 24 h. The SECURE study is a prospective, proof-of-concept, functional non-inferiority, single-centre, randomised, open-label trial to determine if patients with low IMR can be safely discharged when compared to standard discharge policy. The SECURE study will recruit 82 patients with low IMR following successful PPCI. Participants will be 1:1 randomised to either standard discharge timing or very early discharge (within 24 h). The left ventricle ejection fraction will be assessed using cardiac magnetic resonance imaging. A telephone follow-up at 3 months will be arranged. Clinical events are collected as secondary and exploratory safety endpoints. **Conclusions**: The SECURE study will provide proof-of-concept data about the feasibility of using IMR to guide very early discharge following PPCI. If successful, this study will provide data to plan for a larger study to determine the safety of this personalised approach.

## 1. Introduction

Primary percutaneous coronary intervention (PPCI) is the standard treatment option for patients presenting with ST-elevation myocardial infarction (STEMI) [1]. Successful reperfusion therapy using PPCI has resulted in a significant decrease in mortality and a progressive reduction in hospital length of stay (LOS) [2]. As outcomes have improved, earlier hospital discharge has become a priority for both patients and healthcare systems. This was reflected in current guidelines, acknowledging that early discharge is not associated with late mortality and in-hospital length of stay (LOS) of 48–72 h for patients who are considered low risk following successful PPCI should be considered [3]. Nonetheless, objective tools that can define low-risk patients following successful PPCI are currently lacking.

IMR is a quantitative measure that can directly evaluate the status of the myocardium immediately after PPCI. It has the potential to identify patients who are at low risk and may be suitable for early discharge following STEMI presentation. IMR has an important predictive role in patients undergoing PPCI. It correlated with the size of the infarct when measured using peak creatinine kinase, echocardiographic wall motion score, regional 18F-fluorodeoxyglucose (FDG) uptake imaged by positron emission tomography, and infarct volume on cardiac magnetic resonance (CMR) imaging [4,5,6]. Moreover, IMR immediately at the end of PPCI was identified as a reliable predictor of early adverse clinical outcomes [7]. Therefore, IMR may be used as a stratification tool to identify low-risk patients who may be suitable for a ‘step-down’ bed immediately following PPCI, rather than the coronary care unit. This group could also be targeted for an early discharge strategy.

Notably, STEMI patients are kept in hospital to monitor and manage any potential life-threatening complications, as well as to optimise medical therapy and to educate patients on a healthy lifestyle [1,3]. An approach of very early hospital discharge may limit the opportunities to maximise medical treatment, compromising left ventricle recovery following STEMI presentation. Therefore, a comparison of left ventricle function according to hospital discharge strategies would pertain to the role of optimising medical treatment in this setting.

## 2. Rationale of the SECURE Study

Identifying low-risk patients presenting with STEMI who underwent successful PPCI and are suitable for early hospital discharge would be beneficial for patients, physicians, and health care providers. It is well-established that patients feel more supported at home and are often more satisfied with short in-hospital LOS, particularly when discharge planning is well-structured and includes short-term follow-up. Similarly, early hospital discharge will increase efficiency and optimise the use of health care resources, including treating more patients within the same bed capacity.

Determining low-risk STEMI patients who are candidates for early hospital discharge remains to be established. IMR is a reproducible and safe measurement that can be calculated using the guidewire-based thermodilution method, which is widely available in coronary catheterisation laboratories [8]. IMR assessment can be performed immediately following PPCI and can provide prognostic information for patients presenting with AMI [9,10]. Therefore, we set out to study the feasibility of using IMR in patients presenting with STEMI who underwent successful PPCI to guide early hospital discharge. A comparison of patients without major microvascular dysfunction, defined as IMR of equal or less than 40 units, is planned according to their hospital discharge strategies. This means comparing patients with low IMR who are assigned to early hospital discharge, i.e., within 24 h, versus standard in-hospital LOS. We expect that patients with early hospital discharge would have similar left ventricular function on CMR at three months, without increased risk of major adverse clinical events, including death, recurrent myocardial infarction, unplanned revascularisation, readmission to hospital with heart failure, or cardiac arrest, sustained ventricular tachycardia/fibrillation, and cardioverter defibrillator implantation.

## 3. Methods

### 3.1. Study Design

The SECURE study is an investigator-initiated, proof-of-concept, functional, non-inferiority, single-centre, randomised open-label study (ISRCTN56383403, registration date on 5 July 2024). Patients over the age of 18 but less than 90 who underwent successful PPCI with preserved microvascular function and meet the inclusion criteria will be 1:1 randomised to either early hospital discharge, i.e., within 24 h or standard in-hospital LOS. The study will also include a parallel observational registry cohort consisting of non-randomised patients with elevated IMR (>40).

Each participant is expected to remain in the study for 12 months, during which a telephone follow-up is planned at 3 months as well as 12 months. Recruitment is expected to be completed in 24 months with the completion of the study when the last patient undergoes their final clinic follow-up. The study will be subject to an extension should the target study sample size not be achieved by the pre-specified end date to maintain the scientific integrity of the study (Figure 1).

The SECURE study will aim to recruit STEMI patients with (1) large calibre culprit artery of at least 3 mm in diameter, (2) successful angiographic results (Thrombolysis in Myocardial Infarction (TIMI) flow of 3) (irrespective of TIMI flow at presentation and patients with occluded vessel can also be included in the study), and (3) preserved microvascular function identified as IMR ≤ 40. The rationale behind including patients with only a large culprit vessel diameter is to reduce the probability of including patients with relatively small infarcts that can mask any unwarranted effect of early hospital discharge on left ventricle function. This group is likely to have normal left ventricle function and can therefore dilute the treatment effect of optimising medical therapy according to the duration of in-hospital LOS.

### 3.2. Study Setting

The SECURE study is a single-centre study recruiting patients presenting with STEMI who are transferred on the PPCI pathway at the Freeman Hospital in Newcastle upon Tyne.

### 3.3. Study Participants

Patients presenting with STEMI secondary to a culprit vessel of at least 3.0 mm in diameter and undergoing PPCI will be screened for enrolment. Patients need to fulfil the inclusion and exclusion criteria prior to randomisation (Table 1). Following assessment of microvascular function, patients will be 1:1 randomised to either early hospital discharge (within 24 h, experimental group) or standard in-hospital LOS (control group).

### 3.4. Study Procedures

#### 3.4.1. Screening and Assent

Given the emergency setting of the SECURE study, obtaining full informed consent from potential participants prior to any study procedure would not be feasible. Therefore, upon completing the PPCI and after reviewing the inclusion and exclusion criteria, a member of the direct care team will approach the patient whilst they remain inside the catheterisation laboratory. This member will be fully trained in the study aims and its inclusion criteria. After explaining the study and its design, including the risks and benefits of participating in the study, a verbal assent will be obtained after ensuring the patient is clinically stable and judged to have the capacity to understand the study. Importantly, the patient will be informed that there is a chance that they may not meet the inclusion criteria if their microvascular function is deemed impaired according to the IMR assessment. Participants retain the right to withdraw consent, and data will be excluded if full consent is declined. To ensure generalisability of the study, a flow diagram detailing the number of screened and randomised participants will be recorded.

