#### 3.4.3. Randomisation

The SECURE study will only randomise participants who have preserved microvascular function as defined by IMR ≤ 40. Based on previous studies [7,14], we expect that two-thirds of patients with good procedural outcomes, including TIMI 3 flow, will have preserved microvascular function as defined by the SECURE study methodology.

Once microvascular function assessment is performed, patients with IMR ≤ 40 will be 1:1 randomised by means of a web-based randomisation secure method with no stratification block. Blinding or masking of the randomisation group cannot be applied, given the nature of the study. Therefore, patients as well as physicians will be aware of the discharge strategy; however, the analysis of the primary endpoint of left ventricular function will be blindly performed.

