#### 3.4.4. Full Informed Consent and Baseline Data Collection

Following the completion of the PPCI, full written consent will be sought from the patient. Given the nature of the study and the randomisation process, it will be recommended to approach the patient as soon as practical to do so. This will allow the patient to read, reflect and ask any questions related to the study and its procedure.

Upon obtaining a written consent form, baseline clinical data will be recorded. This will include medical history, including the patient’s demographic, procedural and medication details. Routine laboratory blood results, including cardiac troponin level and 12-lead electrocardiogram, will also be recorded.

Patients will undergo standard in-hospital management, including cardiac monitoring, echocardiography, optimisation of medical therapy, and ongoing education.

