### 3.6. Statistical Analysis

The obtained data will be assessed for normality distribution and reported as means (and standard deviation) or medians (and inter-quartile range) accordingly. The primary endpoint of left ventricle ejection fraction will be compared according to the in-hospital LOS groups using an unpaired *t-test* (or Mann–Whitney U test if appropriate). Other cardiac MRI endpoints, such as left ventricle volume and infarct size, will be evaluated using standard statistical tests depending on whether the data will be normally distributed or skewed. The composite clinical endpoints will be assessed with the use of cumulative incidence curves and the estimated Cox proportional hazards model. Each component of the clinical endpoints will be similarly compared between the two groups using chi-square or Fisher’s exact test, as appropriate.

The study is designed to establish the non-inferiority of early discharge compared to standard practice on left ventricle function at three months following STEMI presentation in patients with preserved microvascular function. Previous data suggested that left ventricle ejection fraction was 46 ± 8% in patients presenting with STEMI who underwent an uncomplicated procedure with final TIMI 3 flow and were hemodynamically stable post PPCI [16,17]. Assuming a non-inferiority margin of 5% difference in left ventricle ejection fraction with 80% power at an alpha level of 0.025, a sample size of 82 patients is required (41 patients in each group). An absolute difference of 5% in LVEF was selected based on prior studies, whereas differences in this magnitude are generally considered within the range of measurement variability and unlikely to translate into meaningful differences in clinical outcomes, particularly in haemodynamically stable, low-risk patients [16,18]. Given that 25% of patients presenting with STEMI and TIMI 3 flow will have IMR > 40 [19], and assuming that 5% of included patients will be lost to follow-up, the total sample size is estimated as 122 patients. The primary analysis will be conducted according to the intention-to-treat principle, but per-protocol analysis will also be performed. Missing CMR data will be handled using predefined sensitivity analyses.

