**Figure 2 jpm-16-00207-f002:**
[figure not shown]
An illustrative example of coronary microcirculation assessment using PressureWire™ X. The top row represents a patient with preserved microcirculation function (IMR less than 40), and the bottom row illustrates a patient with impaired microcirculation assessment (IMR above 40). Blue curves show resting transit times and orange shows hyperaemic transit times. Resting as well as hyperaemic pressure and flow indices are displayed on the right side of the Figure.

**Table 1 jpm-16-00207-t001:** Inclusion and exclusion criteria of the SECURE study.

Inclusion criteria
Age 18–90 years
Successful revascularisation with TIMI 3 flow
Haemodynamic stability following PPCI Preserved microvascular function, defined as IMR ≤ 40
Ability to provide verbal consent
Exclusion criteria
Out-of-hospital cardiac arrest
Suboptimal angiographic results
Previous coronary artery bypass grafting
Cardiogenic shock or pulmonary oedema
Planned staged PCI during index admission
Known contraindication to adenosine
Known contraindication for CMR
Pregnancy or breastfeeding

**Table 2 jpm-16-00207-t002:** Primary and secondary objectives of the SECURE study.

Objectives	Outcome Measures	Evaluation Timepoints
Primary Objective Impact of early discharge on left ventricle function in STEMI patients with preserved microvascular function	Left ventricle ejection fraction as estimated on CMR	3 months
Secondary Objectives (a) Safety of early discharge strategy	The composite of all-cause mortality, recurrent myocardial infarction, unplanned revascularisation, readmission with heart failure, cardiac arrest, sustained ventricular tachycardia/fibrillation, and cardioverter defibrillator implantation.	3 and 12 months.
(b) Cost-effectiveness	The potential cost-saving of using coronary physiology to guide early hospital discharge in patients presenting with STEMI and preserved microvascular function.	3 months
(c) Impact on functional status	The severity of angina symptoms and functional status in STEMI patients with preserved microvascular function according to their hospital discharge policy	3 months

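### As written, patients can be randomised before written consent and then excluded if they decline it, which conflicts with the stated intention-to-treat analysis

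*Protocol article*

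**What the plan says.** Section 3.4.1 explains that "obtaining full informed consent from potential participants prior to any study procedure would not be feasible". Verbal assent is therefore taken in the catheterisation laboratory, and IMR is measured on that basis. Section 3.3 requires the Table 1 criteria to be met before randomisation. The only consent criterion in Table 1 is "Ability to provide verbal consent".

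Section 3.4.3 places allocation directly after the measurement: "Once microvascular function assessment is performed, patients with IMR ≤ 40 will be 1:1 randomised". The same section says that "patients as well as physicians will be aware of the discharge strategy".

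Written consent comes in section 3.4.4: "Following the completion of the PPCI, full written consent will be sought from the patient". An approach as early as practicable is recommended, but the section does not tie consent to the moment of allocation.

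On patients who refuse, section 3.4.1 says: "Participants retain the right to withdraw consent, and data will be excluded if full consent is declined". On the analysis, section 3.6 says: "The primary analysis will be conducted according to the intention-to-treat principle". A per-protocol analysis is added, and sensitivity analyses are promised for missing CMR data.

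**The concern.** An intention-to-treat comparison is protected by randomisation only if the patients analysed are those who were randomised. Here a step that removes patients appears to fall after randomisation, when nothing keeps the arm from the patient or from the staff seeking consent. The intervention is the time of going home, so a preference about the allocated arm is a plausible reason to sign or to refuse.

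If refusal depends on both the arm and the patient's condition, the two retained groups are no longer comparable. Should patients who are less well decline early discharge more often, the mean LVEF of that arm would rise and a non-inferiority conclusion would become too easy to reach. The opposite pattern would make it too hard. The provision for missing CMR data does not help, because it cannot restore patients whose data may not be used. The flow diagram in section 3.4.1 is described as recording numbers screened and randomised, so refusals by arm are not promised either.

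**Working it through.** **Order of steps.** No single sentence states that written consent follows randomisation. Four features of the text point that way:

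- Table 1 asks only for verbal consent, and section 3.3 makes Table 1 the gateway to randomisation.
- Section 3.4.3 randomises once IMR has been measured.
- Written consent is described in the section after randomisation.
- Nothing requires written consent before allocation is made or disclosed.

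A site following the text could therefore randomise first. Setting section 3.4.1 (data excluded on refusal) beside section 3.6 (intention-to-treat) then gives a direct conflict for any patient who is randomised and later declines.

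**The plan's own sample size.** Inputs from section 3.6 are SD 8, margin 5, one-sided alpha 0.025 and power 80%; a true difference of zero is taken.

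n per arm = 2 × 8² × (1.960 + 0.842)² / 5² = 40.2, rounded up to 41, so 82 in total. The plan's figure is reproduced. At 41 per arm, SE = 8 × √(1/41 + 1/41) = 1.767 and power = Φ(5/1.767 − 1.960) = 80.8%.

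**Sensitivity to selective refusal (assumed values).** Let d be the share of the early-discharge arm that declines, and D the amount by which decliners' mean LVEF lies below that of patients retained. Nobody declines in the standard arm. The mean of the full early arm is (1 − d)·μ + d·(μ − D) = μ − dD, where μ is the mean of those retained. Excluding decliners therefore raises the arm mean by dD. With 41(1 − d) patients left in the early arm:

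SE = 8 × √(1/41 + 1/[41(1 − d)])

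Type I error at the margin = 1 − Φ(1.960 − dD/SE)

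| d | Early arm left | SE | Shift, D = 4 | Type I error | Shift, D = 8 | Type I error |
|---|---|---|---|---|---|---|
| 5% | 38.95 | 1.790 | 0.2 | 3.2% | 0.4 | 4.1% |
| 10% | 36.90 | 1.815 | 0.4 | 4.1% | 0.8 | 6.4% |
| 15% | 34.85 | 1.843 | 0.6 | 5.1% | 1.2 | 9.5% |

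The shifts are 4% (0.2/5) to 24% (1.2/5) of the margin. The shares correspond to about 2 to 6 patients out of 41. With D = 0 the error stays at 2.5% for every d.

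**Opposite direction.** If the early-arm decliners had the higher LVEF, the sign of the shift reverses. At d = 15% and a gap of 8 points, power under no true difference would be Φ((5 − 1.2)/1.843 − 1.960) = Φ(0.10), about 54% instead of 80.8%.

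**The case against.** The strongest reply is that the order is not actually stated. Section 3.4.4 ties written consent to the end of PPCI rather than to randomisation, and its wish for an early approach refers to the randomisation process, which is compatible with consent before the allocation is released. The statement that patients and physicians know the strategy explains why blinding is impossible; it does not say when the patient is told. The study flow chart might settle the order but is not available here. This stands as a limit on certainty. It does not remove the point, because a text that allows either order needs correcting.

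A second reply is that not using the data of someone who never gave full consent is an ethical safeguard in an approved study. That may well be so, and the exclusion itself is not criticised. It is the reason to place refusals before allocation, where they do no harm to the comparison.

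A third is that a patient unhappy with the allocation may stay in the study and simply not follow it, which the two planned analysis sets cover. That is true for those who sign, but not for those who decline.

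A reader might also infer a loss of power. With 10% refusing in both arms and nobody replaced, power would fall from 80.8% to 76.6%. However, section 3.1 allows recruitment to be extended if the target is not met, so a shortfall is not shown. Replacement would restore the numbers but would not undo selective refusal.

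**Conclusion.** The point holds as a conflict within the document and as an open route to bias. Patients can be randomised on verbal assent and then removed after a refusal made when the arm may be known, while the primary analysis is called intention-to-treat. No analysis plan can repair this afterwards, because the excluded data are gone from the comparison.

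A reader might go further and conclude that refusals do depend on the arm, that data are erased, or that the trial is biased towards non-inferiority with an error rate near 10%. The documents support none of these. They speak of exclusion, they state no dependence on allocation, and they give neither a refusal rate nor an LVEF gap. The 9.5% in the illustration needs 15% refusal in one arm only, with decliners a full SD (8 points) worse, in a population already restricted to TIMI 3 flow, haemodynamic stability and IMR ≤ 40. The range of 3.2–9.5% shows sensitivity under assumed values (constant SD of 8, normal approximation) and is not a prediction.

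**What to change.** Keep verbal assent and IMR measurement as planned. Release the web randomisation only after written consent is signed. If that cannot be done, keep the allocation concealed from patient and staff until it is signed. Only the IMR measurement needs the catheterisation laboratory; allocation to a discharge time does not. State the order explicitly in sections 3.4.3 and 3.4.4.

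For anyone already randomised under the present order, report refusals by arm in the flow diagram and call the analysed set modified intention-to-treat.

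The cost is a protocol amendment and some operational pressure. Consent must be taken early enough for discharge within 24 h to remain possible. Some patients will have IMR measured, decline before randomisation and need replacing, so somewhat more assents and wire studies will be needed to reach 82 randomised patients.
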